When it comes to studies investigating predictors of treatment for stress-related disorders, Kocalevent et al [15] found that symptoms of anxiety but not perceived stress, depressive symptoms, or demographic variables predicted self-rated mental health following treatment for patients diagnosed with AD. In a study investigating burnout, Pallich et al [21] identified emotional competence, but not demographic characteristics, as a predictor of treatment response. However, both of these studies suffer from limited generalizability due to their inadequate description of the treatment offered, the fact that the interventions were conducted in an inpatient setting, and the lack of control groups. In ED patients, one study identified several predictors of treatment outcome following multimodal rehabilitation, including younger age, baseline symptom severity (insomnia, anxiety, and depression), perfectionism, physical activity level, treatment credibility, and a history of sickness absence due to ED [22]. However, the effects of demographics and pretreatment symptoms were so small that they offered limited clinical utility. In sum, at the current stage of research, it is a challenge for clinicians to determine who will benefit from treatment, underscoring the imperative for more sophisticated predictive studies.

Traditionally, prediction in psychiatry has relied on interpretable linear or logistic regression models. The aim has been to identify variables explaining a statistically significant portion of the variance in outcome, under the premise that such variables should inform researchers and clinicians. For example, the presence of previous sickness absence and earlier unsuccessful treatment attempts might lead a psychologist to conclude that a patient requires additional support, possibly extending the treatment duration. Although this approach of identifying predictors has offered some clinical utility, it often falls short in practice; the predictive power of specific variables in isolation is typically inadequate to inform assessment, treatment selection, and adaptations of interventions. Given the inherent complexity of mental disorders, the likelihood of pinpointing strong predictors with clinical utility is small, thus limiting the practical value of this approach [23,24].

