### Objective of the Study

The overall objective of this study is to predict treatment outcomes in patients with stress-related disorders. Due to limitations in existing methods for prediction analyses, this study aims to first evaluate putative predictors using a traditional prediction paradigm, and second to model treatment outcomes using an ML approach. Our primary outcome of interest is responder status after treatment on the Perceived Stress Scale-10 (PSS-10), evaluated using the reliable change index (RCI; further described in the Planned Statistical Analysis and Data Cleaning and Preparation sections). On the basis of earlier research on predictors of treatment outcome, we hypothesize that key predictors will include younger age, education level, baseline symptom severity, treatment credibility, and history of sickness absence. Furthermore, we anticipate that the ML models will outperform a dummy model predicting the majority class and achieve a BACC of ≥67%, thus being indicated clinically useful [28].

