### Outcomes

The primary outcome in this study and the original RCT is PSS-10 [35]. The PSS-10 is a self-report questionnaire developed to evaluate an individual’s perception of life as unpredictable, uncontrollable, and overwhelming. Responses are recorded on an ordinal scale ranging from 0 n*ever* to 4 *very often*, reflecting the individual’s feelings and thoughts over the past month. It contains statements, such as ‘*In the last month, how often have you been upset because of something that happened unexpectedly?’* and sum scores range from 0 to 40. The PSS is the most commonly used outcome measure of stress-management interventions globally [8,36,37]. For this study, a Swedish version of the PSS-10 was used. The PSS-10 has been found to exhibit high internal consistency (Cronbach α=0.84) and adequate construct validity [38]. The PSS-10 was administered digitally through the web-based study platform before randomization to treatment, every 3 weeks during the treatment phase, and at treatment completion (12 weeks). During treatment, the instructions for the PSS-10 were modified to have patients consider the last week instead of the last month. For this study, the sum score of the PSS-10 will be dichotomized into responder or nonresponder after treatment based on the RCI criteria [39] to differentiate between statistically significant change and those attributable to measurement error or natural variability. The PSS-10 baseline and 3-week measurement will also be used as predictors.

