#### Predictor Analysis

For the traditional regression analysis, data will be imputed using the KNN imputer. The imputer, a nonparametric imputation method, works by imputing missing values based on the k-nearest neighbors; in this study *k* will be determined by cross-validation. It uses the Euclidean distance metric to find the nearest neighbors and can be used for both numerical and categorical data. Each missing value is imputed using values from its k-nearest neighbors. After imputation, we will run univariate logistic regressions for each predictor listed in Table 1 using RCI as a target variable. Predictors that are statistically significant in the univariate analyses will then be included in an ablation study, a systematic approach to evaluate feature importance. This method involves iteratively removing each significant predictor from a full model, measuring the change in explained variance, and then reinserting it, thereby quantifying each predictor’s unique contribution to the model’s explanatory power in the context of all other features.

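### The ablation admits only univariately significant predictors, so it cannot give the unique contributions it claims for the week-3 PSS-10 or for hypothesised predictors that miss the screen

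*Protocol article*

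**What the plan says.** Under Predictor Analysis, "we will run univariate logistic regressions for each predictor listed in Table 1 using RCI as a target variable". Significance there decides entry to the next step: "Predictors that are statistically significant in the univariate analyses will then be included in an ablation study". The ablation then works by "iteratively removing each significant predictor from a full model, measuring the change in explained variance" and putting the predictor back. The result is presented as each predictor's unique share of the model's "explanatory power in the context of all other features".

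Three other places matter:
- Objective of the Study names what is expected in advance: "we hypothesize that key predictors will include younger age, education level, baseline symptom severity, treatment credibility, and history of sickness absence". Nothing in the article puts these into the ablation irrespective of the screen.
- Outcomes states: "The PSS-10 baseline and 3-week measurement will also be used as predictors".
- Data Cleaning and Preparation defines the target as a reliable change index on PSS-10 from before to after treatment (alpha 0.83, cutoff −1.96). It removes variables correlated at 0.8 or above from the traditional analysis only.

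**The concern.** A one-at-a-time test asks whether a predictor is associated with response while everything else is ignored. A unique contribution asks what it adds given the rest. Using the first as the entry ticket for the second removes variables whose value appears only once another variable is held fixed.

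This is concrete here because of how the outcome is built. A high week-3 PSS-10 goes with a high baseline, which makes a large drop more likely, and with a high end score, which makes it less likely. The two pull in opposite directions in the univariate regression and separate only when baseline is in the model.

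The screen also applies to the predictors the authors hypothesised. Background says of an earlier exhaustion disorder study that "the effects of demographics and pretreatment symptoms were so small that they offered limited clinical utility". Effects of modest size are the ones a significance screen passes or fails largely by chance. The traditional arm could then give an adjusted contribution for some of its own hypotheses and none for the others.

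**Working it through.** **Sample size.** The article's only sample size figure is for the parent trial (d=0.4, 90% power, alpha .05, 10% attrition). Per arm: 2(1.960+1.282)²/0.4² = 131.4, so 132; total 264; 264/0.9 = 293.3, so 294. That agrees with the stated 300. No figure is given for the screen or the ablation. I use n = 300 × 0.9 = 270 as the analysed sample.

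**Assumed, because the article does not give them:** a two-sided 5% level for the screen, the responder rate, and the PSS-10 SDs and correlations.

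**Two readings of the full model.** If it holds only the predictors that passed, the words about all other features are not true of it. If it holds every Table 1 predictor, only the significant ones are removed and reinserted, so the rest still get no contribution. The mismatch stands on both readings.

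**Week-3 PSS-10.** Let B, W and E be the baseline, week-3 and end scores. The correlation of W with the drop B−E is

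(r_BW·s_B − r_WE·s_E) / √(s_B² + s_E² − 2·r_BE·s_B·s_E).

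Given B, the partial correlation of W with the drop is −(r_WE − r_BW·r_BE)/√((1−r_BW²)(1−r_BE²)), which does not depend on the SDs.

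Worked example, r_BW = r_WE = 0.6 and r_BE = 0.4:
- Equal SDs: the numerator is 0.6 − 0.6 = 0, so the marginal correlation is 0.
- s_B = 5, s_E = 7: (3.0 − 4.2)/√(25+49−28) = −1.2/6.78 = −0.18.
- Partial, both cases: −(0.6 − 0.24)/√(0.64 × 0.84) = −0.36/0.733 = −0.49.

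Simulation, n=270, 1,000 trials per row. For the equal-SD rows the cut is 1.96·√(2(1−0.83)) = 1.14 SD with a mean drop of 1 SD. For the other rows it is a drop of at least 7 points with a mean drop of 5.5. Responders are 41% to 45%.

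| SDs (B/W/E) | r_BW, r_WE, r_BE | Marginal r | Partial r | Passes 5% screen | Significant with baseline |
|---|---|---|---|---|---|
| equal | 0.6, 0.6, 0.4 | 0.00 | −0.49 | about 5% | 100% |
| equal | 0.6, 0.7, 0.5 | −0.10 | −0.58 | 24% | 100% |
| equal | 0.7, 0.6, 0.5 | +0.10 | −0.40 | 23% | 99.9% |
| 5/6/7 | 0.6, 0.6, 0.4 | −0.18 | −0.49 | 62% | 100% |
| 5/6/7 | 0.5, 0.65, 0.4 | −0.30 | −0.57 | 98% | 100% |

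In the third row the marginal association even has the opposite sign to the conditional one. All assumed correlations lie below 0.8, so the collinearity filter would leave the pair in the screen.

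**Hypothesised predictors.** The power of a one-predictor logistic regression per SD is approximately Φ(√(n·p(1−p))·ln OR − 1.96). With n=270 and p=0.4, √64.8 = 8.05. For OR 1.3: 8.05 × 0.262 − 1.96 = 0.15, and Φ = 56%. For OR 1.2, 1.4 and 1.5 the result is 31%, 77% and 90%. Over responder rates of 30% to 50%, OR 1.3 gives 51% to 58%. If all five had OR 1.3 and were independent, at least one would be left out with probability 1 − 0.56⁵ = 94%; at OR 1.5 this is 40%.

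**The case against.** The strongest defence is that the two arms divide the labour. The traditional arm is meant to be simple and interpretable, and joint patterns are left to machine learning. That arm has no univariate screen, keeps highly correlated variables, includes a multivariable elastic net model and reports random forest importance. Each hypothesised predictor also receives its own logistic regression, and the hypothesis is only that it predicts response; no adjusted contribution is promised for each. Much of this stands. A reader might infer that the hypotheses go untested, or that the study as a whole could miss early symptom level; the article does not support either inference. What the defence does not cover is the ablation's own claim. Random forest importance is a different quantity from a model trained on 70% of the data, and does not supply the contribution this section says it will give.

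A second objection is that the cancellation depends on the inputs. That is right. A reader might infer that the week-3 association vanishes as a matter of course. Exact cancellation needs r_BW·s_B = r_WE·s_E, and the article gives no values from which to judge this. With a larger end SD and a closer week-3-to-end correlation, the screen does little harm.

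A third is that Table 1 also pairs baseline and week-3 ISI and the three SMBQ scales, so one might extend the argument to all five pairs. The identity above concerns PSS-10 only, because the other scales are not components of the outcome. The figures here do not carry over to them.

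**Conclusion.** The point holds in a limited form. The entry rule and the description of what the ablation measures are inconsistent as written, and that needs no assumption. The practical loss is conditional. For week-3 PSS-10 the chance of passing the screen runs from about 5% to over 90% across plausible but assumed SDs and correlations, while the association given baseline is detected in about 100%. Entry is therefore governed by nuisance quantities and not by how much the score adds. For the hypothesised predictors, a per-SD odds ratio of 1.3 gives 56% at an assumed 40% responders, so some would probably have no adjusted estimate in the traditional arm. The 94% figure further assumes equal effects and independence and is only indicative. This does not invalidate the univariate results or the machine learning arm. It is a stated rule that gives a worse answer than an easily available alternative.

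**What to change.** Under Predictor Analysis:
- Enter the hypothesised predictors and the baseline/week-3 PSS-10 pair in the ablation model whatever their univariate p-values. Name the Table 1 rows that stand for each hypothesised construct, since baseline symptom severity could mean several scales.
- Add other univariately significant predictors as a second block, labelled exploratory.
- Say that each contribution is relative to the predictors in the model, in place of all other features.
- State the significance level of the screen, and what happens if the collinearity filter would remove one of the prespecified terms.

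The cost is wording and slightly less precise contributions from a few more terms. Five hypothesised predictors plus the pair make about 7 terms if each construct is one row; with 270 × 0.4 = 108 responders that is roughly 15 per term before the exploratory block. The two PSS-10 scores share variance, so the drop on removing either must be read with the other in the model. The article says the data had not been analysed for this study as of March 2025, so, on that account, the change can be made before results are known.

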#### ML Model Development

For an introduction on the technical terms introduced in this section, see the review article by Bzdok and Meyer-Lindenberg [13].

#### Train Test Split

As the ultimate goal of any model is to predict an outcome in unseen data, the ML models will be developed using a training set, and then evaluated on a test set stratified on main diagnosis (AD or ED) and responder status. In total, 70% of the data will be used for selecting predictor variables and training the models, and 30% for testing the prediction accuracy of the models. The choice of 70 to 30 was due to the limited size of our sample, as fewer observations in the testing data makes it difficult to use uncommon predictors. No external validation set is currently available at the time of writing.

#### Standardization and Imputation

Standardization and imputation will be applied on the training and test data separately to avoid data leakage. Numerical data will be standardized and all missing data will be imputed using the KNN imputer.

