#### Hyperparameter Tuning

We will conduct 5-fold cross-validation using randomized search for hyperparameter tuning and training evaluation to enhance the external generalizability and robustness of the results. This process involves defining a hyperparameter space, then randomly selecting a predetermined number of samples—in this case, 10—from this space, and conducting 5-fold cross-validation for each selected set of hyperparameters. Fivefold cross-validation is done by partitioning the data into 5 subsets, training the model on 4 subsets, and validating it on the remaining subset. This process is repeated 5 times, with each subset used exactly once as the validation data. The best performing hyperparameters will be chosen for the final models that are trained and then evaluated on the test set.

The hyperparameter ranges for the LogReg will include C values from 0.01 to 100 and l1_ratio values from 0 to 1. For RF, the parameter ranges will include the number of estimators from 5 to 1200, minimum samples required to split a node from 10 to 200, maximum depths from 5 to 750, and a binary indicator for bootstrapping. For SVM, the parameter range for the randomized search will include regularization parameter C values from 0.01 to 1 and for AdaBoost, the parameter ranges for the randomized search will include the number of estimators, ranging from 1 to 1500, and learning rates from 0.001 to 2.5.

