#### Model Interpretation

The models developed to identify the responder status will be evaluated using BACC, precision and recall, both in the training set obtained through k-fold cross-validation and in the test set. Predictor importance in the RF model will be determined using Scikit-learn’s Feature importance function, which quantifies each predictor’s contribution to the model’s balanced classification accuracy. Area under the curve will be used to assess the models’ capability to distinguish between classes accurately. The approach will aim to provide a clear understanding of the models’ effectiveness and the role of various predictors. Our primary outcome of interest for comparison will be BACC in each model in the test set with the aim that (1) the model should perform better than a dummy model that simply predicts the most common responder status, and (2) that the model should perform 67% BACC or above to be deemed clinically useful [28]. Furthermore, the models will be statistically compared using bootstrap sampling. Specifically, we will generate 5000 bootstrap samples from the test set, calculating the BACC for each model on each sample. The distributions of these bootstrap BACCs will be compared and we will conclude that there is a statistically significant difference between models if the CIs do not overlap.

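### Scaling and imputing the test set from its own data scores the model on a slightly different scale and is undefined for a single new patient; fit both steps on the training data and carry them over

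*Protocol article*

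**What the plan says.** The rule is in the protocol article under Standardization and Imputation: "Standardization and imputation will be applied on the training and test data separately to avoid data leakage". The next sentence gives its scope: "Numerical data will be standardized and all missing data will be imputed using the KNN imputer". Predictor Analysis describes the imputer: "Each missing value is imputed using values from its k-nearest neighbors". It therefore needs a pool of donor patients.

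Train Test Split gives the proportions: "In total, 70% of the data will be used for selecting predictor variables and training the models, and 30% for testing the prediction accuracy". It opens with the purpose of the split: "As the ultimate goal of any model is to predict an outcome in unseen data". Model Interpretation makes the test set decisive: "Our primary outcome of interest for comparison will be BACC in each model in the test set". The criteria there are to beat a majority-class dummy model and to reach a BACC of at least 67%. Comparison to Prior Work foresees later external validation and trials of the models as decision support.

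No section says that means, SDs or imputation donors learned in the training set are carried over to the test set.

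**The concern.** A prediction model consists of its preprocessing as well as its coefficients or tree splits. To estimate how it performs in unseen patients, the whole chain is fixed on the training data and then applied unchanged. The sentence in the protocol, followed literally, does something else:

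- Coefficients and split points learned on the training scale are applied to values centred and scaled with different constants.
- Missing test values are filled from the smaller test cohort, not from the training patients.
- The same patient could receive a different prediction if the other test patients were different.
- A single new patient has no cohort from which to take a mean, an SD or neighbours.

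At stake is what the primary performance figure describes. Test-set BACC would be the BACC of a cohort-dependent procedure, not of a fixed model that could be used on the next patient.

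**Working it through.** **Inputs from the protocol.** N = 300; 70/30 split; predictors kept with up to 20% missing; threshold of 67% for test BACC. The protocol gives no figure for the effect of preprocessing, so there is none to reproduce.

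**Set sizes.** With all 300 patients: 0.70 × 300 = 210 training and 0.30 × 300 = 90 test. If 10% have no usable outcome (an assumption, borrowed from the RCT's expected attrition), 270 remain: 189 and 81.

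**Shift in scale.** For a predictor with SD 1, the chance difference between training and test means has SD √(1/n_test + 1/n_train):

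- 210/90: √(1/90 + 1/210) = 0.126
- 189/81: √(1/81 + 1/189) = 0.133

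The relative standard error of the test-set SD is about 1/√(2(n − 1)): 7.5% at n = 90 and 7.9% at n = 81. Stratifying the split on diagnosis and responder status makes the mean shift somewhat smaller for predictors related to those two.

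**Donor pool.** For a predictor with 20% missing, about 0.8 × 90 = 72 test patients could act as donors, against 0.8 × 210 = 168 training patients.

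**One new patient.** The patient's own mean is the observed value, so the numerator is x − x = 0. The SD is 0, and there are no donors. The standardised value is 0/0, and a missing value cannot be filled.

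**Effect on BACC (illustrative).** The same trained model was scored on a test set preprocessed with training parameters and on one preprocessed from its own data. All inputs below are assumptions.

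*Scaling only:* 60 predictors, ridge-type logistic model, 189/81 patients, 400 splits. Mean BACC was 0.600 and 0.602 under the two rules. Predicted class changed for 4.7% of test patients (0.047 × 81 ≈ 4). The average change in BACC in a single split was 1.9 points.

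*Scaling and KNN imputation:* 55 predictors with correlation 0.3, ridge logistic model, k = 5, 210/90 patients, 300 runs per scenario, cut-off at the training responder rate.

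| Responder rate | Missing | Mean BACC, training-fitted | Mean BACC, own-fitted | Class changes | 95% range of difference (points) | Opposite sides of 67% |
|---|---|---|---|---|---|---|
| 30% | 0% | 0.604 | 0.604 | 4.6% | −4.2 to +6.1 | 6.3% |
| 30% | 10% | 0.601 | 0.602 | 7.7% | −6.5 to +5.8 | 9.3% |
| 30% | 20% | 0.593 | 0.597 | 10.2% | −7.4 to +7.1 | 9.7% |
| 50% | 0% | 0.610 | 0.612 | 4.9% | −3.4 to +4.4 | 8.3% |
| 50% | 10% | 0.596 | 0.597 | 7.7% | −5.7 to +5.6 | 4.0% |
| 50% | 20% | 0.599 | 0.596 | 10.2% | −5.8 to +6.6 | 7.7% |
| 40%, half the effect sizes | 10% | 0.542 | 0.541 | 8.3% | −5.9 to +6.1 | 1.7% |

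The mean differences run from −0.003 to +0.004, and none exceeds twice its Monte Carlo standard error (0.0012 to 0.0021). The SD of the difference is 2.1 to 3.7 points.

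**Comparison with sampling error.** Take sensitivity and specificity both at 0.67 and 81 test patients. The standard error of BACC is ½ × √(0.67 × 0.33/n₁ + 0.67 × 0.33/n₀):

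- equal classes (40.5 each): 0.052
- 30% responders (24.3 and 56.7): 0.057

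The added noise is smaller than this.

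**The case against.** The strongest reply is that the wording is loose. The protocol says the steps are applied separately, not fitted separately. It names scikit-learn, where the usual practice is to fit on training data and transform each set, and it promises documented code. The authors may intend exactly that. This stands as a possible explanation. But the literal reading is the plainer one, nothing elsewhere corrects it, and an analyst who followed the sentence would build the other procedure.

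Several stronger readings are tempting, and the document does not support them:

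- **That the rule leaks test data into training.** It does not. No test values or outcomes reach the fitted model, so the aim named in the sentence is met.
- **That the reported BACC will be inflated.** The simulations show noise in both directions and no systematic shift.
- **That preprocessing is stated to come before cross-validation.** Hyperparameter Tuning only defines the folds ("training the model on 4 subsets, and validating it on the remaining subset") and does not mention preprocessing. The order could be inferred only from the order of the sections.
- **That KNN imputation in the traditional analysis is stated to use unscaled data.** Predictor Analysis says "It uses the Euclidean distance metric to find the nearest neighbors and can be used for both numerical and categorical data". It neither states nor rules out prior scaling, which a condensed article may leave to the full plan.
- **That the procedure cannot be externally validated.** An external cohort could be scaled and imputed within itself. Only the single patient is undefined, and the protocol places decision support in later research.

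It is also fair to say that the effect is modest beside the sampling error of a test set of 81 to 90 patients.

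**Conclusion.** The point holds in a limited form. As written, the preprocessing rule makes test-set BACC the performance of a transformation that depends on the test cohort and is undefined for one new patient. That does not fit the stated goal of prediction in unseen data.

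The cost is added error, not bias. About 5% to 10% of test patients change predicted class, and a single-split BACC moves by about 2 points on average. The two versions fall on opposite sides of 67% in about 2% to 10% of runs. With one split and one fixed threshold this can matter if the result lies near 67%, but it is smaller than the sampling error of about 5 to 6 points.

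The shift of about 0.13 SD follows from the split alone. The BACC figures rest on assumed responder rates, missingness, effect sizes, correlation and k, and on a ridge-type logistic model. The random forest, support vector machine and AdaBoost classifiers were not simulated. The sentence should be corrected before the analysis, but the error does not invalidate the design.

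**What to change.** Replace the first sentence of Standardization and Imputation with: *The scaler and KNN imputer are fitted on the training data only and applied unchanged to the test data.*

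A scikit-learn Pipeline that holds the scaler, the imputer and the classifier does this. If the Pipeline is what is passed to the randomized search, both steps are also refitted within each cross-validation training fold.

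If this is what the authors already intend, only the wording changes. Otherwise the cost is a few lines of code, with no new data and no new software. The protocol states that the data had not been analysed for this study as of March 2025, so the correction could be made before results are known.
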